## Abstract

**Background:**

In the last few years, several nicotine products have become available as alternatives to smoking tobacco. While laboratory and limited clinical studies suggest that these devices are less toxic compared to classic tobacco cigarettes, very little is known about their epidemiological impact. Visiting the emergency department (ED) often represents the first or even the only contact of patients with the health care system. Therefore, a study conducted at the ED to assess the impact of these products on health can be reliable and reflect a real-life setting.

**Objective:**

The aim of this noninterventional observational study (SMOPHED study) is to analyze the association between the severity of clinical presentation observed during ED visits among patients using various nicotine products and the subsequent outcomes, specifically hospitalization and mortality.

**Methods:**

Outcomes (hospitalization and mortality in the ED) will be examined in relation to various patterns of nicotine products use. We plan to enroll approximately 2000 participants during triage at the ED. These individuals will be characterized based on their patterns of tobacco and nicotine consumption, identified through a specific questionnaire. This categorization will allow for a detailed analysis of how different usage patterns of nicotine products correlate with the clinical diagnosis made during the ED visits and the consequent outcomes.

**Results:**

Enrollment into the study started in March 2024. We enrolled a total of 901 participants in 1 month (approximately 300 potential participants did not provide the informed consent to participate). The data will be analyzed by a statistician as soon as the database is completed. Full data will be published by December 2024.

**Conclusions:**

There is substantial debate about the harm reduction potential of alternative nicotine products in terms of their smoking-cessation and risk-reduction potential. This study represents an opportunity to document epidemiological data on the link between the use of different types of nicotine products and disease diagnosis and severity during an ED visit, and thus evaluate the harm reduction potential claims for these products.

**International Registered Report Identifier (IRRID):**

PRR1-10.2196/54041

## Introduction

Smoking-related diseases are a well-known group of pathologies that are responsible for 8 million deaths per year globally [1]. Despite numerous restrictions, taxation, and communication campaigns, there are still more than 1.3 billion smokers globally. Quitting smoking remains one of the most cost-effective methods to reduce health risks. However, the success rate of smoking cessation methods remains low in real-world settings [2-5]. Additionally, a substantial proportion of smokers are unwilling to use smoking cessation services but would prefer switching to a less harmful alternative product [6,7]. In the last few years, several alternatives to smoking nicotine products have become available, which are commonly referred to as electronic nicotine delivery systems (ENDS), namely e-cigarettes and heated tobacco products (HTPs). While laboratory and limited clinical studies suggest that these products reduce exposure to toxins and may thus reduce health risks [8-12], very little is known about their epidemiological impact.

Several studies have demonstrated a high proportional cigarette smoking prevalence in patients presenting to the emergency department (ED), which is higher than the prevalence in the general population [13-19]. This is expected considering the disease burden caused by smoking, which might result in more ED visits for smokers compared to nonsmokers. Current smoking as well as smoking relapse were found to be significantly associated with ED visits [20-24]. Access to the ED often reflects the first or the only contact of patients with the health care system; thus, the ED visit represents an opportunity to record smoking and nicotine use patterns. However, no studies have systematically recorded use patterns for ENDS in relation to ED visits. Considering the growing popularity of these products and the limited epidemiological evidence on their health effects, a detailed recording of use patterns for all nicotine products is important to monitor their use prevalence, health care system burden, and epidemiological impact.

The National Early Warning Score (NEWS) is a standardized tool used for assessing and responding to acute illness in patients admitted to the ED [24]. The NEWS is based on a straightforward aggregate scoring system, assigning scores to routine physiological measurements taken when patients either present at or are monitored in the hospital. The scoring system is based on six key physiological parameters: (1) respiration rate, (2) oxygen saturation, (3) systolic blood pressure, (4) pulse rate, (5) level of consciousness or new confusion (alert, verbal, pain, unresponsive [AVPU] scale), and (6) temperature.

For patients accessing the ED, the NEWS aids triage nurses in determining the appropriate urgency level for patient examination, which is represented by color codes. This stratification is based on the severity and urgency of the patient’s condition.

The aim of this study is to accurately document the patterns of smoking and nicotine product use, including ENDS, in patients visiting the ED. A key focus is to investigate whether the use of ENDS is associated with any measurable differences in disease severity and outcomes compared to conventional tobacco smoking among these patients.

## Methods

### Study Design

The Smoking or Nicotine Phenotype and Severity of Clinical Presentation at the Emergency Department (SMOPHED) study is an observational study with no intervention or randomization, analyzing the association between the patient’s health condition during an ED visit as well as the outcome (hospitalization and death) and different patterns of nicotine products use. Specifically, the study will explore relevant associations according to the smoking and ENDS product use status (current, former, and never use). The pilot phase of the study will take place at a single clinical center, aiming to evaluate its feasibility and analyze the results. Upon successful completion, there are plans to expand the study into a multicenter format involving a national network comprising 10-12 EDs.

### Study Population

Inclusion and exclusion criteria are summarized in Textbox 1. Participants will be recruited among patients presenting at the ED of Policlinico Teaching Hospital of Catania, Italy, in 1 month during the diurnal shift. Only patients that access the ED for a nontraumatic reason will be screened, since it is unlikely that smoking or use of other nicotine products can have any causal effect on accident incidence and subsequent diagnosis. The study will take place during daytime working hours owing to organizational constraints. Typically, our ED admits approximately 70-80 patients for nontraumatic issues during a daytime shift, which runs from 8 AM to 8 PM.

We calculated the expected sample size for the study based on available national and regional statistics, providing a practical approach to estimating the study’s sample size. The current and former smoking rates in Sicily are estimated at 22.5% and 13.3%, respectively [25], while the combined prevalence of combustion-free products use (e-cigarettes and HTPs) stands at approximately 5% [26]. Considering the annual Catania ED access rate of 80,000 (monthly access rates of 6000-6500) [27], we anticipate recruiting no less than 1500 current smokers and 1000 former smokers per month. Additionally, we expect to enroll no less than 350 users of combined e-cigarettes/HTPs per month (dual usage is estimated at approximately 50% of the total). Since approximately 70 patients per day access the ED during the diurnal shift for nontraumatic reasons, we expect to enroll approximately 2000 participants in 1 month.

Inclusion and exclusion criteria for study participation.Inclusion criteriaAdult (aged≥18 years)Ability to understand and sign the informed consent formExclusion criteriaAccessed the emergency department for a traumatic accidentPregnancy

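### The forecast group sizes rest on all emergency-department accesses, cannot fit in the planned total of about 2000, and are 3.3 to 3.8 times what the plan's own rates give for that total

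*Protocol article*

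**What the plan says.** All the sizing is in one paragraph of the Study Population section (Protocol article, Methods). It gives three rates: "The current and former smoking rates in Sicily are estimated at 22.5% and 13.3%, respectively", and "the combined prevalence of combustion-free products use (e-cigarettes and HTPs) stands at approximately 5" per cent. It names as its base the "annual Catania ED access rate of 80,000 (monthly access rates of 6000-6500").

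From these it derives the group forecasts: "we anticipate recruiting no less than 1500 current smokers and 1000 former smokers per month", and "we expect to enroll no less than 350 users of combined e-cigarettes/HTPs per month". It adds that "dual usage is estimated at approximately 50% of the total".

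The paragraph then changes base. Starting from about 70 nontraumatic patients per daytime shift, it concludes that "we expect to enroll approximately 2000 participants in 1 month". The Methods part of the Abstract repeats this total. The Results part of the Abstract reports the outcome: "We enrolled a total of 901 participants in 1 month", with about 300 people declining consent.

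**The concern.** The group forecasts and the total describe the same month of recruitment, so they should agree, and they do not. Accesses to the ED include nights, trauma and repeat visits. Enrolment is limited to daytime, nontraumatic, consenting patients at their first visit.

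This paragraph is the article's only basis for the size of the study. The hypothesis under Endpoint and Outcomes is a lower NEWS with ENDS use than with cigarette smoking, and the analysis keeps exclusive and dual users apart. Precision therefore depends mainly on the smallest group, exclusive e-cigarette/HTP users. The same section makes multicentre replication conditional on the hypothesis being confirmed. A reader who takes the forecast at face value will expect a much firmer answer than the design can give.

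**Working it through.** **Inputs (Study Population unless noted).** Rates of 22.5% (current), 13.3% (former) and about 5% (e-cigarette/HTP); dual share about 50%; 80,000 accesses a year or 6000-6500 a month; flow of 70-80 per daytime shift; planned total about 2000. From Results: 901 enrolled and about 300 refusals.

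**Step 1: does the forecast fit the total?** 1500 + 1000 = 2500, which is 2500/2000 = 125% of the sample, with no never users yet. The 350 should not be added, because dual users are also current smokers and exclusive users are mostly former smokers.

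**Step 2: reproduce the stated counts.** Expected count = base × rate.

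| Base | Current, 22.5% | Former, 13.3% | E-cigarette/HTP, 5% |
|---|---|---|---|
| 6000 per month | 1350 | 798 | 300 |
| 6500 per month | 1463 | 865 | 325 |
| 80,000/12 = 6667 | 1500 | 887 | 333 |
| Planned 2000 | 450 | 266 | 100 |
| Enrolled 901 | 203 | 120 | 45 |
| **Stated, at least** | **1500** | **1000** | **350** |

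The 1500 reproduces exactly at 80,000/12, which shows that the base was all accesses. The other two do not reproduce even there: 1000 needs 1000/0.133 = 7519 accesses a month, and 350 needs 350/0.05 = 7000.

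**Step 3: size of the error against the plan.** At 2000: 1500/450 = 3.3; 1000/266 = 3.8; 350/100 = 3.5. With half of the e-cigarette/HTP users dual, about 50 are not dual users, against 175 implied by 350.

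**Step 4: the total of 2000.** 70 × 28 = 1960 and 70 × 30 = 2100, so 2000 follows from the daily flow. It then needs 2000/2100 = 95% of that flow, or 2000/(80 × 30) = 2000/2400 = 83% at the upper flow. Refusals were about 300 of 901 + 300 = 1201, or 25%. At 75% consent, the two flows give 2100 × 0.75 = 1575 and 2400 × 0.75 = 1800.

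**Step 5: effect on precision.** Take exclusive users as half of ENDS users, and smokers net of dual users. The two-group detectable difference in SD units (two-sided 5%; 80% power is my assumption) is 2.80 × √(1/n₁ + 1/n₂).

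- Stated counts, 1325 vs 175: 0.225 SD
- At 2000, 400 vs 50: 0.420 SD, ratio 0.420/0.225 = 1.9
- At 901, about 181 vs 22.5: 0.626 SD, ratio 0.626/0.225 = 2.8

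The ratios do not depend on the SD. The article gives no SD for NEWS. For an assumed SD of 1.5 to 3, the 901 figure is 0.626 × 1.5 to 0.626 × 3, or about 0.9 to 1.9 NEWS points.

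**The case against.** The strongest defence is that this is a practical recruitment forecast for a single-centre pilot, not a power calculation. No analysis, endpoint or error rate depends on it. That is true, and it limits what follows: the article states no power or effect size for ENDS versus smoking, so one cannot say that a promised power has been missed. But feasibility is a stated aim of the pilot, and a forecast that exceeds its own total is wrong as written.

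Four stronger readings are tempting and are not supported.

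- *None of the counts follows from the plan's rates.* The 1500 does, on 80,000/12. The main fault is the base; on that base 1000 is about 13% high and 350 about 5% high.
- *The ENDS group is overstated nearly eightfold.* That figure (350/45 = 7.8) sets a forecast against the enrolment later achieved, which the article reports openly. Against the plan itself the ratio is 3.5.
- *The total of 2000 is itself an arithmetic error.* It follows from 70 a day. It is optimistic about consent, which is a different criticism.
- *The protocol promises 175 exclusive users.* It gives only the dual share. The rest need not all be former smokers, since the Statistical Analysis section allows for never-smoking ENDS users.

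It can also be said that 450/266/100 use general-population rates, while the Introduction and Discussion say smoking is more common among ED patients. The true number of current smokers may well be higher. That does not rescue the stated counts, because no prevalence lets current and former smokers together make up 125% of a sample.

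**Conclusion.** The point holds. The paragraph contradicts itself because the group forecasts and the total use different bases. Against the planned 2000 the stated counts are 3.3 times (current), 3.8 times (former) and 3.5 times (e-cigarette/HTP) too high, assuming that the article's rates apply to those enrolled. The excess of 2500 over 2000 needs no assumption at all.

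The total leaves almost no room for refusal at 70 a day, whereas about a quarter of those asked declined. Refusal alone does not account for the shortfall, since only about 1201 people are recorded as enrolled or declining; the article does not explain the rest.

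The loss of precision for ENDS versus smokers, about 1.9-fold at 2000 and 2.8-fold at 901, rests on half of ENDS users being exclusive and on a simple two-mean comparison. The planned Kruskal-Wallis test and adjusted regression will not match it exactly. Any figure in NEWS points depends on an SD that the article does not give.

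**What to change.** In Study Population:

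1. Delete the minimum counts of 1500, 1000 and 350. Restate the expected counts on the eligible base, about 450, 266 and 100 for 2000 participants. Note that these use general-population rates and that the article itself reports higher smoking prevalence in the ED.
2. Keep the planned 2000 visible, here and in the Abstract, and report the 901 enrolled beside it as a shortfall. Do not overwrite the plan with the result.
3. Give the actual group counts from the questionnaire when available. Until then, about 203, 120 and 45 is only what the stated rates would give for 901; it should not become a new forecast.
4. State that the ENDS versus smoker comparison is much less precise than the present counts imply. Give the relative figures (about 1.9 and 2.8 times), and show any absolute figure over a range of NEWS SDs, labelled as an assumption.

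The cost is wording, and stated figures that look less favourable. No extra patients and no change to study conduct are needed.

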### Ethical Considerations

The study will be conducted according to the principles of Good Clinical Practice and the Declaration of Helsinki. Ethical clearance for this protocol was obtained through the ethical review board “Comitato Etico Catania 1” at Policlinico Teaching Hospital of Catania (84/2023/PO del Registro dei pareri del CE) on April 17, 2023. If any amendments to this protocol are required, the chief investigator will be responsible for the decision to amend the protocol and for deciding whether an amendment is substantial or nonsubstantial. Any substantial amendments will be submitted to the research ethics committee for approval before implementation. Informed consent from study participants will be obtained by the investigators through relevant forms. A dedicated website will be created for the study. This website will respect the General Data Protection Regulation policy. Every study team member will access the site with a personal and unique ID and password. The website will create two different databases to guarantee participants’ privacy. The first database will record the fiscal code of the participant and will assign a unique ID. The second database will anonymously record the data from each participant using only the participant’s ID. It is necessary to create two databases so that additional information on outcomes or other missing data will be recorded at a later time.

Patients will be asked for authorization to use their clinical data in an anonymous format, in accordance with the current privacy directives related to access to the ED. The informed consent model will be shown to participants who must be able to understand and sign it as an inclusion criterion to participate in the study. All collected informed consent forms will be stored at the ED of Policlinico Teaching Hospital of Catania. No financial or other incentives will be provided to the participants.

### Data Collection

On arrival at the ED, each patient undergoes a triage phase. A nurse is usually responsible for evaluating the severity of the health condition and the priority for clinical assessment (unless the patient enters the ED by ambulance under a red code). The nurse usually performs this task by collecting vital signs and recording the patient’s medical history. This information is then used to assign a color code representing the priority for further assessment. The patient then waits for the medical evaluation in a dedicated room where nurses can monitor the clinical condition of all attending patients. Participants who meet the inclusion criteria will be recruited during this phase and will be administered an electronic questionnaire (see Multimedia Appendix 1) about their smoking and nicotine product use habits and their medical history. This questionnaire serves to typify the patient’s use phenotype and quantify exposure to each product.

In addition to the questionnaire, medical data recorded at the triage phase, such as the NEWS, heart rate, blood pressure, blood oxygen saturation, respiratory rate, temperature, and fraction of inspired oxygen, will be collected.

After the assessment and management of each patient in the ED, the final diagnosis, final disposition, and color code at discharge or admission to a ward will be recorded (see Table 1). To avoid compromising the health of patients with severe disease requiring urgent medical attention, potential participants who arrive at the ED under a red code (ie, with a severe acute illness) will be asked to participate only after they are stabilized (ie, the questionnaire, NEWS, and vital signs will be recorded later).

Based on the responses to the questionnaire, participants will be divided in the following 5 smoking subgroups to facilitate analysis: (1) current tobacco smoker, (2) former tobacco smoker, (3) former tobacco smoker now using e-cigarettes and HTPs (exclusive use), (4) current tobacco smoker also using e-cigarettes and HTPs (dual use), and (5) never smokers or e-cigarette/HTP users.

After 1 month, data in the electronic case report form (eCRF) will be extracted for the statistical analysis.

Since the ED is usually very crowded, four study team personnel will work on the study and will screen and recruit patients during the waiting period before the medical examination. The study team will interview potential participants in a dedicated room within the ED area to guarantee privacy. The initial survey will last approximately 5 minutes per patient. This is a reasonable time to collect product use information from each participant. After the medical visit and final disposition, compilation of the eCRF will be completed as provided by the study protocol, with each study member collecting all necessary information about the patients’ outcome (discharge or admission to a ward) by the end of their shift. Some patients may stay in the ED beyond the length of a diurnal shift; in such a case, the data will be collected the day after their arrival. Some patients might access the ED two or more times during the study. To avoid double entries, only the first visit will be included for analysis in the study. The eCRF database will reply with an error if we try to recruit a patient with the same fiscal code a second time (a fiscal code is a unique identifying code in Italy, and it is mandatory to be recorded for each patient during the triage phase in the ED).

**Table 1 table1:** Data to record in the electronic case report form.

Data type			Value/units
NEWS^a^ calculated at the patient’s triage phase (conventionally, patients with an acute condition will be recorded as being at high risk, corresponding to NEWS>7)			0-17

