### Endpoint and Outcomes

The primary endpoint of the study is the association between the NEWS and product use phenotypes. Our hypothesis is that use of ENDS may be associated with a lower NEWS compared to cigarette smoking. If our hypothesis will be confirmed, the study will be replicated as a multicenter study to validate our findings.

Secondary outcomes will be hospital admissions (vs discharge) and length of stay in the ED and in the hospital (if admitted). Moreover, we will compare the prevalence of acute diseases known to be related to smoking between groups, specifically stroke, acute myocardial infarction, peripheral artery diseases, chronic obstructive pulmonary disease, asthma, and respiratory infections.

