This study has several limitations. The brief period of recruitment and the use of only one study site may introduce sampling bias due to seasonality and locality. Therefore, this study may have limited generalizability to all Italian EDs. However, as mentioned above, this represents a pilot study with the purpose of further expanding the protocol to more regions and several EDs from other hospitals. While it is possible to verify exposure to tobacco smoke by measuring exhaled carbon monoxide and exposure to nicotine by measuring salivary cotinine, logistical and financial restrictions within the short duration of an ED presentation, as well as the urgent nature of attendance requested in the ED, preclude us from performing an objective assessment of the smoking status. Although self-report of smoking status has been shown to be accurate in the ED setting [17], a systematic review (despite including studies outside the ED setting) showed some discrepancy between self-report and objective assessment [43]. In addition, determining nicotine exposure would not help to distinguish between the use of tobacco cigarettes and noncombustible nicotine products. Moreover, the responses to questions on past smoking and nicotine use habits may be introducing recall bias. Finally, the exclusion of patients in a critical state who need urgent care will be compensated by a subsequent request to participate in the study once they are stabilized.

In conclusion, this study protocol addresses the need for additional epidemiological evidence on the effects of ENDS on health, with clinical endpoints. The ED setting represents an opportunity to record smoking and nicotine habits, assess the burden of different products, and provide guidance for interventions at both the personal and systematic level.

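### For red-code arrivals the primary endpoint, NEWS, has no single measurement rule: the text says after stabilisation, Table 1 says at triage or as a conventional value above 7

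*Protocol article*

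**What the plan says.** Endpoint and Outcomes: "The primary endpoint of the study is the association between the NEWS and product use phenotypes". The hypothesis is that "use of ENDS may be associated with a lower NEWS compared to cigarette smoking", and replication as a multicentre study depends on its being confirmed.

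Three places in the article bear on how NEWS is obtained:

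- **Data Collection, general rule.** The study collects "medical data recorded at the triage phase, such as the NEWS, heart rate, blood pressure" and the other vital signs.
- **Data Collection, red code.** For "potential participants who arrive at the ED under a red code (ie, with a severe acute illness"), the request to take part waits until after stabilisation, and "the questionnaire, NEWS, and vital signs will be recorded later". The same section says that the nurse's triage evaluation is the usual route except for patients brought in by ambulance under a red code.
- **Table 1.** NEWS is the score calculated at triage, on a 0-17 field, with this addition: "conventionally, patients with an acute condition will be recorded as being at high risk, corresponding to NEWS>7". Vital signs are listed as triage recordings, with no exception for red code.

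Statistical Analysis plans mean (SD) for numerical data, a Kruskal-Wallis test for NEWS, and regression of NEWS on product use (type not given).

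The limitations paragraph of the Discussion says that "the exclusion of patients in a critical state who need urgent care will be compensated by a subsequent request to participate in the study", made after stabilisation. It does not mention that the timing of their NEWS changes.

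**The concern.** Red-code patients supply the upper end of the NEWS distribution, and they are the ones for whom the article gives no single rule. Depending on which place staff follow, the same patient could be entered with a triage score, with a lower score taken after treatment, or as a conventional value above 7. Nothing says which governs.

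A score taken after stabilisation describes treated physiology, whereas the study asks about severity at presentation. If one product group has more red-code arrivals than another, lowering the scores of those patients alone removes part of the difference that the study looks for. The decision to go on to a multicentre study rests on this comparison, so attenuation matters. The convention in Table 1 raises a different problem: it gives a range where a numeric analysis needs a value, and its trigger is not defined in a population that attends because of acute illness.

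**Working it through.** The article states no figure on this point, so there is none to reproduce. The check is a comparison of the text followed by an illustration.

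**1. Text.** The two rules differ in three respects.

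| | Data Collection (red code) | Table 1 |
|---|---|---|
| Who | red-code arrivals, glossed as severe acute illness | patients with an acute condition, undefined |
| When | after stabilisation | at triage |
| What is entered | a recorded score | a conventional value above 7 |

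On an integer 0-17 field, above 7 means any of the ten values 8 to 17.

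**2. Loss from a score after stabilisation.** Assumptions, none from the documents: non-red mean 1.5 in both groups; red-code arrival NEWS 8 to 9; stabilised NEWS 2 to 5; red-code share 10% in smokers and 5% in ENDS users.

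Mean difference = (share in smokers − share in ENDS users) × (red NEWS − non-red NEWS)

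| Arrival | Stabilised | Difference at arrival | Difference after stabilisation | Lost |
|---|---|---|---|---|
| 8 | 5 | 0.05 × 6.5 = 0.325 | 0.05 × 3.5 = 0.175 | 46% |
| 9 | 5 | 0.05 × 7.5 = 0.375 | 0.175 | 53% |
| 8 | 2 | 0.325 | 0.05 × 0.5 = 0.025 | 92% |
| 9 | 2 | 0.375 | 0.025 | 93% |

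**3. Dependence on the non-red means.** In step 2 the shares cancel from the fraction lost only because the non-red means are equal. Take instead non-red means of 1.8 (smokers) and 1.5 (ENDS users), with red-code NEWS falling from 9 to 3:

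- Shares 10%/5%: arrival (0.9 × 1.8 + 0.1 × 9) − (0.95 × 1.5 + 0.05 × 9) = 2.520 − 1.875 = 0.645. Stabilised: 1.920 − 1.575 = 0.345. Lost: 47%.
- Shares 20%/10%: 0.99 becomes 0.39. Lost: 61%.
- Shares 10%/10%: 0.27 stays 0.27. Lost: 0%.

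**4. Effect on the planned test.** A simulation used 450 smokers and 100 ENDS users (22.5% and 5% of 2000, the prevalences and target in Study Population), with 1000 runs per scenario. Further assumptions: non-red NEWS Poisson with mean 1.5, capped at 7; red arrival NEWS uniform on 8-13; a fall of 5 or 8 points on stabilisation. Each cell gives the mean difference, then the Kruskal-Wallis rejection rate at 0.05.

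| Red-code shares | Arrival score | After stabilisation, fall 5 | After stabilisation, fall 8 | All red-code set to 8 |
|---|---|---|---|---|
| 5%/5% and 10%/10% | about 0; 4-5% | about 0; 4% | about 0; 5% | about 0; 4-5% |
| 10%/5% | 0.45-0.46; 11-12% | 0.21; 11% | 0.05; 6% | 0.32-0.33; 11-12% |
| 20%/10% | 0.90-0.91; 35-37% | 0.40; 33% | 0.10; 7% | 0.65-0.66; 35-36% |

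So a score after stabilisation roughly halves the mean difference or nearly removes it. The rank test loses little while treated scores still exceed most non-red scores (fall 5) and most of its power when they do not (fall 8). A common top value leaves the rank test almost unchanged. That result relies on non-red scores being capped at 7, below the common value.

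**5. Arbitrary value in a numeric analysis.** With shares 10%/5% and non-red mean 1.5, entering 8 for every red-code patient gives 0.05 × (8 − 1.5) = 0.325; entering 17 gives 0.05 × (17 − 1.5) = 0.775. Both entries satisfy Table 1.

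**The case against.** The strongest reply is that the two rules may be complementary. Table 1 does not name red code; equating its undefined term with the severe acute illness of Data Collection is an inference, though a likely one. Recording later could mean later entry of triage values in the eCRF, and the convention could be meant for patients who bypass nurse triage and so have no triage score. This stands as far as it goes: a reader might infer a flat contradiction, and the text does not prove one. It does not supply a rule either. The article does not establish that a triage score exists to be copied for a red-code ambulance arrival. If the convention covers these patients, the instruction to record their NEWS later has no purpose.

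A reader might also infer that both rules distort the primary comparison. The documents do not support that. Both apply to every phenotype alike, bias needs red-code shares or falls in score that differ by phenotype, and the documents report neither. The planned univariate test is rank-based, and a common top category hardly moves it. Where shares differ, the effect of a treated score is attenuation, which does not favour the ENDS hypothesis.

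Finally, the number stored for the conventional value and the regression type are details that an article may leave to a fuller document. That is fair. The timing of the primary measurement is different, because the article states it, and states it in two ways.

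**Conclusion.** The point holds in limited form. The primary endpoint has no single rule for the most severe patients, and the red-code instruction, followed as written, yields a score that does not measure severity at presentation. If red-code shares differ by phenotype, that score attenuates a difference between groups; with equal shares and equal falls there is no bias. The convention in Table 1 is nearly harmless for the Kruskal-Wallis test, but means and any numeric regression would depend on the value chosen.

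The size cannot be known from the documents. The 46-93% loss is an illustration that rests on arrival scores of 8-9, stabilised scores of 2-5 and equal non-red means. It should not be read as independent of the red-code shares: once non-red means differ, the loss ranged from 0% to 61% in the examples shown. The Discussion's statement that a later request compensates is too strong. It can recover consent but not the arrival measurement, and because Study Population requires ability to understand and sign, patients who die or remain unable to consent do not enter.

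**What to change.** Reconcile Data Collection with Table 1 under one measurement rule before analysis:

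1. For every participant, compute NEWS from the first vital signs charted at ED arrival, abstracted from the chart after consent. Do not use values after stabilisation for the primary endpoint.
2. Replace the undefined trigger in Table 1 with a defined one: red-code arrivals with incomplete arrival vital signs.
3. Place those patients in a top ordered category, analysed by rank or ordinal methods and not as a number, and repeat the analysis without them.
4. In the Discussion, state that later consent does not restore the arrival measurement and does not bring in patients who die or remain unable to consent. The change in measurement does not cure that selection, so it should stand as a limitation.

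Cost: changes to protocol and eCRF wording, and retrospective chart abstraction for the red-code participants among the 901 already enrolled. Some arrival vital signs may be incomplete. The documents do not say how often, so the number falling into the top category should be reported by phenotype.
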